### Participants

The inclusion criteria are as follows: (1) age 18–80, (2) clinical diagnosis of stroke (cerebral infarction, primary intracerebral haemorrhage, subarachnoid haemorrhage) within 6 months before enrolment, (3) Fugl-Meyer Assessment of the Upper Extremity (FMA-UE) score 8–47, (4) Mini-Mental State Examination (MMSE) score ≥ 22 and compliance with the interventions and (5) provision of written informed consent [20, 21].

The exclusion criteria are as follows: (1) more than one stroke (patients with previous transient ischaemic attack could participate); (2) other current significant impairment of the upper limb, e.g. fixed contracture, shoulder subluxation, or recent fracture; (3) severe visual deficits or unilateral spatial neglect; (4) diagnosis likely to interfere with rehabilitation or outcome assessments, e.g. traumatic brain injury, meningitis and epilepsy; and (5) current participation in another upper limb rehabilitation trial [21, 22]. Of note, patients with contraindications to transcranial magnetic stimulation and functional magnetic resonance imaging (e.g. pacemakers, claustrophobia, implanted metal, implantable electronic devices) will NOT be excluded but will NOT receive corticospinal excitability or fMRI examination.

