### Outcomes

All outcomes will be measured at baseline, post-intervention (at 4 weeks) and follow-up (at 12 weeks) with no charge. The primary outcome will be mean change in the Fugl-Meyer Assessment for Upper Extremity (FMA-UE) score. This assessment examines arm movement, coordination and reflexes, and the results are represented as a 3-point ordinal scale score with a maximum of 66 points. The FMA-UE is a reliable and valid scale with which to measure upper limb motor impairment after stroke, with higher scores indicating better motor function [24].

Secondary outcomes will be the mean change in Action Research Arm Test (ARAT) score, modified Barthel Index (MBI), kinematic metrics, resting motor threshold (rMT) and motor evoked potentials (MEP), functional magnetic resonance imaging (fMRI) and safety outcomes.

The Action Research Arm Test (ARAT) evaluates 19 tests of arm motor function, including four subscales: grasp, grip, pinch and gross movement. Each test is given an ordinal score of 0, 1, 2 or 3, with the total score ranging from 0 to 57, with higher values indicating better arm motor status and dexterity [25].

The modified Barthel Index (MBI) is an assessment tool formulated to examine the level of independence in the basic ADL and comprises 10 categories: feeding, personal hygiene, toilet use, bladder control, bowel control, bathing, dressing, chair/bed transfer, ambulation, and stair climbing [26].

We will use kinematic metrics (Inertial Measurement Unit, IMU, Noraxon USA Inc.) to evaluate the movement smoothness (peak speed, time to peak speed, number of movement units and path ratio) and performance (pointing time and pointing accuracy) during the finger-to-nose test. The instrumented kinematic assessment can provide good sensitivity for detecting motor performance that is not captured by the clinical scales [27, 28].

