Corticospinal excitability will be measured using resting motor threshold (rMT) and motor evoked potentials (MEP) from the abductor pollicis brevis (APB) muscles [29]. Patients will be instructed to sit in a comfortable chair with their hands resting on their lap during the evaluations. Transcranial magnetic stimulation (TMS MagVenture® MagPro R30 Denmark) will be performed using a figure-eight coil placed tangentially in a posterior–anterior plane at a 45° angle from the midline over the hotspot. The rMT is defined for each hemisphere as the minimal stimulator output intensity that elicits MEPs with peak-to-peak amplitudes of at least 50 μV from the contralateral APB muscle in at least five of ten trials. MEPs will be sampled during TMS at 110% rMT and will be kept constant during the following evaluations. The MEP will be recorded as zero if not evocable [30, 31].

Functional magnetic resonance imaging (fMRI) acquisition and pre-processing will be conducted as follows. Scanning will be on the same 3.0 Tesla MR scanner (Discovery LS MR 750; GE Healthcare, Chicago, IL, USA), including acquisition of high-resolution anatomical images, followed by two fMRI series of two hemiplegic-sided motor tasks: finger-to-nose motion (task 1) and finger-to-nose motion sequence observation and execution (task 2). The range of motion for each task is not controlled but rather self-determined. Each series contains 30-s epochs that alternate rest with 0.03-Hz movement. We will acquire functional images using the T2*-weighted gradient echo planer imaging sequence, which measures the blood oxygen level dependence (BOLD) signal. Scanning parameters will include 43 axial 3-mm-thick slices of the whole brain per repetition, 204 volumes/series, TR = 3000 ms and TE = 30 ms, matrix size = 72 × 72 and FOV = 216 × 216 mm^2^. During the fMRI scan, subjects will view a guidance video displayed on the screen. The video will run continuously with a 0.03-Hz movement cycle that is green during rest epochs, yellow during task 1 epochs and red during task 2 epochs. For all conditions, each series will consist of 5 cycles alternating between a 30-s baseline block (fixation cross) followed by a 30-s task block, yielding a total duration of each fMRI run of 10 min. Before entering the scanner, subjects will practice the paradigm and an investigator will observe subject movements during scanning to verify task compliance [32].

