### Statistical analyses

All statistical analyses will be performed using SPSS software (version 21.0, IBM Corporation, Chicago, IL). To assess the normal distribution of quantitative data, the Shapiro-Wilk test will be employed (*P* > 0.05). Continuous variables will be presented as the mean (SD) for normal distributions and median for non-normal distributions and categorical variables will be presented as frequencies or percentages. Baseline data between groups will be compared using Student’s t-test for continuous variables and the chi-square or Fisher’s exact tests for categorical variables. A *P* value < 0.05 will be considered indicative of statistical significance. All analyses will be carried out based on the intention-to-treat principle, with missing data calculated using multiple imputation. Within-group differences will be assessed using paired t tests for the normally distributed data and Wilcoxon-signed rank test for the non-parametric equivalent test. When comparing the two patient subgroups at each time point, Student’s *t* test (for continuous data) and Fisher’s exact test (for categorical data) will be implemented. When examining the effect of the randomization procedure over time, two-way repeated measures analysis of variance (ANOVA) will be conducted to examine the time-treatment group interaction, with time as the within-group variable and treatment group as the between-group variable.

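### Multiple imputation is prescribed for all missing data, although rMT does not exist when no MEP can be evoked and contraindicated patients are never examined by TMS or fMRI

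*Protocol article*

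**What the plan says.** Four statements in the protocol article bear on this.

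- **Statistical analyses:** "All analyses will be carried out based on the intention-to-treat principle, with missing data calculated using multiple imputation". No outcome or type of absence is carved out. The same section offers a rank test for within-group comparisons only; between groups, continuous data go to Student's t-test and repeated measures ANOVA.
- **Outcomes, rMT:** the threshold is the "minimal stimulator output intensity that elicits MEPs with peak-to-peak amplitudes of at least 50" μV, in at least five of ten trials, for each hemisphere.
- **Outcomes, MEP:** "The MEP will be recorded as zero if not evocable". The sampling intensity depends on the threshold: "MEPs will be sampled during TMS at 110% rMT and will be kept constant during the following evaluations".
- **Participants:** patients with a contraindication to TMS or fMRI "will NOT be excluded but will NOT receive corticospinal excitability or fMRI examination". The Outcomes section nevertheless plans every outcome at baseline, 4 weeks and 12 weeks.

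rMT, MEP and fMRI are secondary outcomes and carry the trial's aim of exploring neurological mechanisms.

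**The concern.** Imputing a missed visit assumes that a value exists and that similar patients with data can stand in for it. Neither assumption suits an rMT that cannot be obtained. The patient was examined and no threshold was found, and the reason is severe corticospinal damage. A missing-at-random model fitted to evocable patients will give that patient a threshold typical of someone less impaired. If one arm recovers better, the arms differ in how many patients are affected, and the estimated effect on rMT is pulled towards zero.

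Contraindicated patients raise a different question. Their TMS and fMRI values are absent by design at every visit, including baseline. Imputed values for them have no measurement of that kind from the patient behind them.

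**Working it through.** The documents give no figure on this point, so there is none to reproduce. The check has two parts.

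**1. Which absent values does the rule reach?**

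| Value | Why absent | Rule in the plan | Reached by imputation as written? |
|---|---|---|---|
| MEP amplitude, not evocable | no response | coded zero | no |
| rMT, not evocable | undefined, since no MEP meets the criterion | none | yes |
| rMT, MEP and fMRI, contraindicated | not examined, by design | no analysis set given | yes, on a literal reading |
| Any outcome, missed visit | dropout or missed assessment | multiple imputation | yes, as intended |

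The protocol foresees non-evocable patients, because it codes their MEP. It does not say what happens to their rMT, so the general rule applies by default.

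**2. What does imputation do to the group difference in rMT?** This was simulated with assumed inputs; only the 44 per arm comes from the Sample size section.

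- Two arms of 44; 2,000 runs; 10 imputations from a normal linear model on group and one covariate.
- Latent rMT = 80 + effect × group − 8 × covariate + error, in percent of maximum stimulator output. The covariate is standard normal and the error SD is 15.
- Mechanism A: 15% of patients unmeasured for reasons unrelated to outcome, as for contraindications.
- Mechanism B: rMT unobtainable when the latent value exceeds 100% of output, as for non-evocable patients.

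| True difference | A, imputed | B, share unobtainable | B, imputed | B, observed cases only |
|---|---|---|---|---|
| -8 | -8.01 | 8.5% | -6.36 | -6.00 |
| 0 | -0.02 | 11.9% | 0.03 | 0.05 |

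Attenuation under B with imputation is 1 − 6.36/8 = 20.5%. With observed cases only it is 1 − 6.00/8 = 25%.

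Monte Carlo error is small. The total SD is √(8² + 15²) = 17, so the standard error of one difference is about 17 × √(2/44) = 3.6. Over 2,000 runs this is about 3.6/√2000 = 0.08, apart from imputation noise. The gap of 8 − 6.36 = 1.64 is far larger.

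Two things follow. The bias depends on why the value is absent and on there being a real effect. And simply dropping non-evocable patients is no remedy, since it attenuated slightly more than imputation did.

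**The case against.** The other side has a fair case. The article gives one sentence on missing data, and outcome-specific analysis sets or exemptions may stand in an analysis plan that is not shown. The Data monitoring and management section treats missing values as problems to be queried with the centres, so planned non-examination might not count as missing data at all. The outcomes are secondary, the share of patients affected is not given, and imputation did slightly better than observed cases in the simulation. All of this limits the weight of the point. It does not remove it: the published rule covers all analyses, and the rMT definition leaves a foreseen group of patients with no value and no rule.

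Stronger readings are tempting, but the document does not support them:

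- **Kinematics.** A reader might infer from the FMA-UE entry floor of 8 that some patients cannot do the finger-to-nose test and would have pointing times imputed. The document neither says that any patient will be unable nor withholds the test from anyone.
- **Bias from contraindicated patients.** Pacemakers, implants and claustrophobia are plausibly unrelated to motor outcome, and mechanism A showed no bias (-8.01 against -8). Imputation there is uninformative, but not shown to be biased.
- **MEP amplitude.** A non-evocable MEP is already zero, so it is not imputed. What remains is the t-test on data with a spike at zero.
- **Reversal of direction.** Suppose 26 patients per arm are evocable at a mean of 60%, and 8 in one arm and 2 in the other regain an MEP at 90%. Means among evocable patients are (26×60 + 8×90)/34 = 67.1 and (26×60 + 2×90)/28 = 62.1, so the better arm looks worse. But these are observed-case, post-treatment means on assumed inputs. The plan specifies mean change, and the 26 patients with both measurements change by zero in each arm. The example does not measure imputation bias.

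**Conclusion.** The point holds for rMT, and as a matter of consistency for the TMS and fMRI outcomes of contraindicated patients. The imputation rule as published conflicts with the definition of rMT and sits badly with the decision to keep contraindicated patients unexamined. For rMT, imputing from evocable patients can attenuate a true group difference, by about 20% in the simulation. That size rests on an assumed threshold distribution, an assumed effect of -8 points, about 8.5% unobtainable values, one hemisphere and a single post-treatment value rather than change. The actual share of non-evocable patients is unknown, and the attenuation will vary with it. With no true effect, no bias appeared, so the simulation gives no sign of a spurious difference. It would be wrong to conclude that the mechanistic outcomes as a whole will be biased. The primary FMA-UE analysis is not touched.

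**What to change.** Amend the Statistical analyses section, or state in the analysis plan, that:

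1. Multiple imputation does not apply to rMT when TMS was performed and no MEP could be evoked, nor to TMS or fMRI values not collected because of a contraindication.
2. TMS and fMRI outcomes are analysed in patients without a contraindication to the examination concerned, determined before randomisation, with that denominator shown.
3. Non-evocable rMT is kept in the analysis as a value above maximum output, hence worst rank, in a rank-based between-group comparison. No numeric change exists when either end is above maximum, so the comparison should rank the values at 4 and 12 weeks.
4. MEP presence or absence in the affected hemisphere is reported alongside rMT.
5. Zero-coded MEP amplitude is compared between groups by a rank test, not Student's t-test.

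The cost is wording, smaller and labelled denominators for TMS and fMRI, and an rMT summary based on ranks instead of means. The prespecified secondary outcomes stay in place. The text is best settled before outcome data are examined; 12 patients had been enrolled when the article was submitted.

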### Intervention

Stroke patients in all groups will require multidisciplinary medication and rehabilitation; hence, their routine treatment programmes will continue as usual with the additional 4-week intervention. The intervention will be delivered at the same frequency and duration in the three groups: 45 min daily, 5 days/week for 4 weeks. The same therapists and therapy assistants will deliver all the intervention sessions at each centre [12].

Participants in the CT group (conventional therapy) will receive the therapist-mediated arm intervention using conventional therapy techniques, such as muscle strengthening, stretching, arm exercises or gross-motor training, fine-motor training and functional task practice. This therapy matches that in the other groups with respect to schedule and the form and intensity of movements. The programmes in the conventional group will progress to meet the patient’s training goals.

The EXO group (exoskeleton therapy) will receive intensive task-specific training in the three-dimensional workspace of the human arm involving shoulder (flexion/extension, horizontal abduction/adduction, external/internal rotation) and elbow (flexion/extension, pronation/supination) movements (Armule®, Intelbot Intelligent Machine Co., Ltd., Wuhan, China). Each training session consists of exercises in the following order: 5-min passive mode plus 15-min assist-as-needed mode for twice with a 5-min break between intervals. In the passive mode, the exoskeleton manipulates the upper limb in a three-dimensional trajectory predetermined by the therapists according to the patient’s goals. In the assist-as-needed mode, the patients practice games and ADL training programmes dedicated to shoulder and elbow movements. When the patient is unable to complete the tasks actively, assistive force will supply the upper extremity with passive movement to the target positions.

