### Sample size

The sample size was calculated by considering the primary outcome measure as the reference: a mean difference of 5 points in the FMA-UE between the AOT-EXO group and CT group and 3 points between the AOT-EXO group and EXO group with a standard deviation of 5.0 [33]. Based on multiple comparisons significance level of 1.67% and a power of 0.8, a sample size of 40 per group will be needed. Assuming that 10% patients loss to follow-up, we will choose a sample size of 44 participants for each group and 132 participants in total. The sample size calculation was performed with PASS 2008 software.

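### Paired within-arm tests of FMA-UE change cannot answer a between-arm question, and no listed test isolates the AOT-EXO contrasts on change

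*Protocol article*

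**What the plan says.** Outcomes defines the primary quantity: "The primary outcome will be mean change in the Fugl-Meyer Assessment for Upper Extremity (FMA-UE) score". It is measured at baseline, 4 weeks and 12 weeks.

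Statistical analyses then lists three kinds of test that bear on FMA-UE:

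- **Within arm.** "Within-group differences will be assessed using paired t tests for the normally distributed data", with the Wilcoxon signed-rank test as the alternative for non-normal data.
- **Between two arms.** Student's t test, introduced by "When comparing the two patient subgroups at each time point". As worded, this compares scores at a visit, not change from baseline. The text does not say which two of the three arms are meant.
- **All arms over time.** A "two-way repeated measures analysis of variance (ANOVA) will be conducted to examine the time-treatment group interaction".

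One general rule covers the section: a P "value < 0.05 will be considered indicative of statistical significance". The paired tests are not called descriptive, and no test is singled out for the FMA-UE conclusion.

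Sample size rests on pairwise between-arm differences: "a mean difference of 5 points in the FMA-UE between the AOT-EXO group and CT group", and 3 points between AOT-EXO and EXO, with an SD of 5.0 and a 1.67% level for multiple comparisons.

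Two other sections bear on what a within-arm change means. Participants requires "clinical diagnosis of stroke (cerebral infarction, primary intracerebral haemorrhage, subarachnoid haemorrhage) within 6 months before enrolment". Intervention says of all groups that "their routine treatment programmes will continue as usual with the additional 4-week intervention".

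**The concern.** A paired test asks whether one arm's mean change is zero. The trial asks whether AOT-EXO adds something to exoskeleton therapy alone or to conventional therapy. These are different questions. In patients in the first months after stroke, who continue routine rehabilitation and receive an active 4-week programme in every arm, some gain is to be expected whether or not the arms differ.

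Two misreadings are then possible. If the common gain is large, every arm improves significantly, and the AOT-EXO result can be mistaken for evidence of benefit. If the common gain is small, some arms pass 0.05 and others do not by chance, and that pattern can be mistaken for a difference between arms.

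The listed between-arm tests do not fully close the gap. The pairwise test is on levels, not on the change that defines the primary outcome. The test that is on change does not say which arms differ. A reader who wants one P value attached to AOT-EXO and to mean change finds it only in the paired test.

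**Working it through.** The plan gives no figure on this point, so there is none of its own to reproduce. (The 40 per group is used here as given. It does not follow from the stated inputs: a 3-point difference with SD 5, two-sided 1.67% and power 0.80 needs 59 by the normal approximation. That is a separate matter.)

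**Inputs from the article.** 40 evaluable patients per arm (Sample size) and level 0.05 (Statistical analyses), taken as two-sided because sidedness is not stated.

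**Assumptions.** A mean gain g, the same in all arms, and an SD of change s. The article gives no expected gain and does not say that its SD of 5.0 is the SD of change. So s is taken as 5, 7.5 and 10, and g is varied.

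**Formulas.** The paired t statistic has 39 degrees of freedom and noncentrality g × √40 / s. Let p be the probability that one arm's test is significant. For three independent arms with the same g and s:

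- all three significant: p³
- some but not all significant: 1 − p³ − (1 − p)³

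Example, g = 3 and s = 5: the noncentrality is 3 × 6.325 / 5 = 3.79, which gives p = 0.959. All three: 0.959³ = 0.88. Disagreement: 1 − 0.882 − 0.0001 = 0.12.

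Results when the arms do not differ:

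| SD of change | Common gain | One arm significant | All three significant | Arms disagree |
|---|---|---|---|---|
| 5 | 1 | 23% | 1% | 54% |
| 5 | 1.5 | 46% | 10% | 74% |
| 5 | 2 | 69% | 33% | 64% |
| 5 | 3 | 96% | 88% | 12% |
| 5 | 5 | >99.9% | about 100% | about 0% |
| 7.5 | 3 | 69% | 33% | 64% |
| 7.5 | 5 | 98% | 95% | 5% |
| 10 | 3 | 46% | 10% | 74% |
| 10 | 5 | 87% | 66% | 34% |

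With 44 per arm and a gain of 3 points, the one-arm figures are 97%, 74% and 49% for SDs of 5, 7.5 and 10. The number of dropouts therefore matters little.

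**Between-arm contrast.** With the same gain g in both arms, the expected difference in change is g − g = 0 for every g. The rejection rate stays at the nominal level whatever the common recovery.

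**What the listed between-arm tests deliver.** With three arms and three visits the interaction has (3 − 1) × (3 − 1) = 4 numerator degrees of freedom. It can be significant because EXO differs from CT, or because arms differ only between 4 and 12 weeks. It does not estimate either contrast in Sample size. The t test at a visit is valid under randomisation, but it compares scores that still carry the patients' baseline spread, and eligibility allows FMA-UE from 8 to 47.

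**The case against.** The strongest reply has four parts.

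- **The interaction is a between-arm test of change.** This stands. With baseline and a single later visit it is equivalent to comparing change scores across arms. A reader might infer that the paired test is the only test applied to change; the article does not support that. What remains is that the interaction, as an omnibus test, does not isolate the two sized contrasts.
- **Nothing says efficacy will be concluded from the paired tests.** This also stands. Sample size treats efficacy as a between-arm question. A reader might infer from the general 0.05 rule that within-arm significance will count as proof of benefit. No sentence says so; the risk is one of misreading.
- **A significant paired test is not an error if patients do recover.** Correct. A reader might infer that these tests have an inflated false-positive rate, or that they turn significant without any treatment effect. Neither follows: the null of no change would be false, and every arm receives active therapy. The defensible statement is that they can be significant with no difference between arms.
- **The size depends on undocumented inputs.** Correct. With SD 5 and a gain of 1 point, significance in a given arm is unlikely (23%). The two misreadings also belong to different settings: at a 5-point gain with SD 5 the arms almost never disagree, and the 74% figure is close to the highest that three tests can reach (0.75 at p = 0.5).

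It can also be said that ranking the analyses is commonly left to a statistical analysis plan. That is fair for the ranking. But the paired tests, and the t test at each time point as the only pairwise comparison, are stated choices.

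**Conclusion.** The point holds in limited form. The within-arm tests cannot inform the trial's question, and the pairwise between-arm test that could do so is specified on levels, without adjustment for baseline, while the primary outcome is change. At 40 per arm and a common gain of 3 points, each paired test is significant in 96%, 69% or 46% of trials for an SD of change of 5, 7.5 or 10, with no difference between arms. The identical arms disagree on significance in 12%, 64% or 74% of trials respectively. These figures rest on an assumed gain, an assumed SD of change, a two-sided 5% level and approximately normal changes.

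The trial does have a valid between-arm test of change, and its design is not in doubt. This is a desirable improvement to the analysis text, not a defect that threatens the trial.

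**What to change.** In Statistical analyses:

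1. Replace the within-arm paired and signed-rank tests of FMA-UE by the mean change in each arm with a 95% confidence interval and no P value.
2. Replace the unadjusted t tests at each time point, for FMA-UE, by the pairwise contrasts AOT-EXO vs CT and AOT-EXO vs EXO, adjusted for baseline FMA-UE (ANCOVA or an equivalent model), and state that efficacy conclusions on FMA-UE rest on these. With baseline as a covariate, the contrast is the same whether the response is the follow-up score or the change, so the primary outcome need not be redefined.
3. Keep the interaction, if wanted, as a supporting analysis.

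The level for the contrasts should be stated at the same time, since Sample size uses 1.67% and Statistical analyses 0.05; that is a separate question.

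The change needs only new wording. Baseline and follow-up FMA-UE are already collected, and neither the design nor the sample size changes. The article reports 12 of 132 patients enrolled at submission. The downside is that the within-arm P values customary in rehabilitation papers would not be shown.

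### The stated between-group tests are not matched to the two pairwise FMA-UE change contrasts that the trial is sized on, and they leave baseline unadjusted

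*Protocol article*

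**What the plan says.** **Outcome.** Under Outcomes: "The primary outcome will be mean change in the Fugl-Meyer Assessment for Upper Extremity (FMA-UE) score". It is measured at baseline, 4 weeks and 12 weeks, and neither later visit is singled out as primary.

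**Sizing.** Under Sample size the trial rests on two pairwise effects. The larger one is "a mean difference of 5 points in the FMA-UE between the AOT-EXO group and CT group". The smaller one, which isolates action observation, is given as "3 points between the AOT-EXO group and EXO group". One spread serves for both: each effect is taken "with a standard deviation of 5.0". The significance level is 1.67%, power is 0.8, and 40 per group is the result (44 with dropout). The text does not say whether 5.0 is the SD of change or of the score at a visit.

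**Analysis.** Under Statistical analyses there are two between-group methods for efficacy. One is a Student's t-test: "When comparing the two patient subgroups at each time point". The other is an omnibus test: "two-way repeated measures analysis of variance (ANOVA) will be conducted to examine the time-treatment group interaction". The threshold is 5% throughout. The 1.67% level does not reappear, no baseline covariate is named, and the two subgroups are not identified.

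**Entry range.** Under Participants: "Fugl-Meyer Assessment of the Upper Extremity (FMA-UE) score 8–47". No SD of the score is given.

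**The concern.** The outcome and the sizing describe one analysis, a comparison of FMA-UE change between named pairs of groups at 1.67%. The analysis section describes others.

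The question that separates this trial from a plain robot trial is whether AOT-EXO differs from EXO. An interaction over three groups and three visits has (3 − 1) × (3 − 1) = 4 degrees of freedom and gives no pairwise estimate or interval. The method that could address the pair is the t-test. It does not say which pair is meant, and its wording most naturally suggests scores at each visit. With entry scores spread over 39 points, an unadjusted comparison of visit scores could be far noisier than SD 5.0 implies, and it would carry any chance baseline difference into the result.

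**Working it through.** **1. The plan's own figure.** Inputs from Sample size: SD 5, alpha 0.0167 (taken as two-sided; the text does not say), power 0.80.

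n per group = 2 (z₁₋α/₂ + z₀.₈)² (SD/δ)² = 2 (2.394 + 0.842)² (5/δ)² = 20.9 × (5/δ)²

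- δ = 5: 21 per group (23 with the t distribution).
- δ = 3: 59 per group (60 with the t distribution).

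The stated 40 is not reproduced. At 40 per group, power is 98% for 5 points and 60% for 3 points. These are the reference values below.

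**2. The t-test on visit scores.** The SD at a visit is not in the document, so it is an assumption. A uniform spread over 8–47 would give 39/√12 = 11.3; I use 8 to 12, with 5 and 7 for comparison. Power is from the noncentral t with 78 degrees of freedom, critical value 2.447 and noncentrality δ / (SD × √(2/40)). For example, at SD 10 and δ = 3 the noncentrality is 3/2.236 = 1.34 and power is 14%.

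| Visit-score SD | Power, 3 points | Power, 5 points | n per group for 80%, 3 points |
|---|---|---|---|
| 5 | 60% | 98% | 60 |
| 7 | 30% | 77% | 116 |
| 8 | 23% | 64% | 151 |
| 10 | 14% | 42% | 235 |
| 12 | 10% | 29% | 337 |

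**3. The t-test on change scores.** If 5.0 is the SD of change, the SD 5 row applies: 60% and 98%, with nothing lost.

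**4. Baseline adjustment.** Assume the SD of change is 5 and the score SD is the same at both visits. Then the correlation is r = 1 − 25/(2 SD²) and the ANCOVA residual SD is SD × √(1 − r²).

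| Visit-score SD | r | Residual SD | Power, 3 points | Power, 5 points |
|---|---|---|---|---|
| 8 | 0.805 | 4.75 | 65% | 99% |
| 10 | 0.875 | 4.84 | 63% | 98% |
| 12 | 0.913 | 4.89 | 62% | 98% |

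Against a change-score t-test the gain is 2 to 5 percentage points for 3 points. Against a visit-score t-test it is large.

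**5. The interaction test.** Stable differences between patients cancel in a within-patient contrast, so the visit-score SD does not matter here. By simulation (40 per group, change SD 5, correlation 0.7 between the two changes, 5% level):

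- Group changes 0, 2, 5 (CT, EXO, AOT-EXO): significant in about 99% of runs.
- Group changes 0, 5, 5, so that AOT-EXO equals EXO: still significant in over 99% of runs.

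The test is powerful, but a significant result does not bear on AOT-EXO against EXO.

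**6. Chance baseline imbalance.** With 40 per group the SE of a baseline difference is SD × √(2/40): 1.79 at SD 8 and 2.53 at SD 11.3. Two given groups would then differ at baseline by 3 points or more in about 9% and 23% of trials. An unadjusted visit comparison leaves that difference in.

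**The case against.** A reader might infer that the planned analysis as a whole loses most of its power. The document does not support this, for three reasons.

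- The interaction test works on within-patient change and keeps high omnibus power.
- The loss in the t-test rests on a visit-score SD that is not stated. An eligibility range is not an SD, and 5.0 is not labelled as the SD of change. At a visit SD of 5 the loss is nil, and for the 5-point contrast more than half the power goes only from an SD of about 10.
- The t-test may be meant for change. The outcome is defined as change, and baseline comparison has its own sentence in the analysis section. Nothing there says raw scores.

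A reader might also infer that the time-point t-test is biased or aimed at the wrong quantity. It is not. Under randomisation, the difference between groups at a visit has the same expectation as the difference in change; it is only less precise.

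Finally, this is a condensed article, and covariate lists and interval reporting are commonly left to an analysis plan. Their absence alone is no finding.

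All of that stands, and it limits the size of the point. It does not remove the point, because the article commits to specific tests. Those tests refer to two subgroups in a three-group trial, use 5% where the sizing used 1.67%, and include an omnibus test that cannot separate the planned pairs.

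**Conclusion.** The concern holds in a limited form. The stated tests are not tied to the outcome and contrasts on which the trial is sized. The interaction cannot show whether AOT-EXO differs from EXO, and the t-test neither names its pair nor uses the baseline FMA-UE that is collected.

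The cost in power is conditional. If the t-test is applied to visit scores, with a score SD of 8–12 and a change SD of 5, power falls from 60% to 23–10% for 3 points and from 98% to 64–29% for 5 points. If it is applied to change, that loss disappears and adjustment adds only a little.

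It would be tempting to conclude that baseline adjustment rescues the trial. It does not: at score SDs of 8–12, the 3-point contrast stays at about 62–65%, because 40 per group is too small on the stated inputs. That is a separate sample size error.

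**What to change.** In Statistical analyses, make the primary analysis a baseline-adjusted model of FMA-UE: either ANCOVA at the primary visit, or a mixed model over weeks 4 and 12 with treatment, visit, treatment-by-visit, baseline FMA-UE, baseline-by-visit and centre. Name one primary time point. Report AOT-EXO vs CT and AOT-EXO vs EXO (and EXO vs CT if it is kept) with confidence intervals at the 1.67% level used in the sizing. Treat the time-point t-tests and the omnibus interaction as supportive only, and replace the reference to two subgroups with the named pairs.

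In Sample size, state whether SD 5.0 is the SD of change, of the visit score or of a baseline-adjusted residual.

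The cost is wording. The data are already collected, and the named software fits these models. The change should be made before outcomes are compared by group. The shortfall for the 3-point contrast needs its own correction.
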